## Abstract

**Background:**

Sub-threshold depression is common and could impair function, as well as increase the risk of developing major depression. Despite evidence of efficacy for electroacupuncture (EA) and counseling in the treatment of sub-threshold depression, the sample size is insufficient and the level of evidence remains low. This study aims to evaluate the effectiveness of sub-threshold depression treatments by comparing the treatment effects among EA, counseling, and combination therapy, as well as to further study their mechanism.

**Methods:**

This study is a multicenter, randomized, single blind clinical trial that will be conducted in settings at four clinical centers in China. The randomized controlled trial (RCT) will examine the effectiveness of EA intervention, compared with counseling and combination therapy. A total of 138 sub-threshold depression patients (18 to 55 years of age with Beck Depression Inventory (BDI-II) score ≥ 14 points and Hamilton Depression Scale (HAMD-17) score: 7 points ≤ HAMD total score <17 points) will be recruited. The participants will be randomly assigned to receive the above treatments. The interventions will be delivered over a 6-week period (EA: 3 times a week for 6 weeks; 30 min a session. Counseling: once a week for 6 weeks; 50–60 min a session). The primary outcome measure will be the HAMD-17; BDI-II. The secondary outcome measures will be: Self-rating Depression Scale (SDS), Self-rating Anxiety Scale (SAS), and Pittsburgh Sleep Quality Index (PSQI). The assessments will occur at baseline, 2, 4, and 6 weeks and a follow-up period. Recruitment will commence in March 2020 and is anticipated to occur over a 2-year period.

**Discussion:**

This study intends to conduct a multicenter randomized controlled trial to compare the effectiveness among EA, counseling and the combined therapy in the treatment of patients with sub-threshold depression, and to further study the mechanisms of effect.

**Chinese Clinical Trial Registry registration:**

www.chictr.org.cn/, identifier ChiCTR1900028530.

## Introduction

Sub-threshold depression is commonly referred to as “subsyndromal depression” or “minor depression,” and it is mainly characterized by depressive symptoms for at least 2 weeks that fall short of full diagnostic criteria for major depressive disorder (MDD) or dysthymia (1). Epidemiological surveys show that the percentage of 1-year prevalence sub-threshold depression in the general population is 8.4% (2). In China, the incidence of sub-threshold depression among high school students is 22.9%, while college students have reached 36.56% (3, 4). Having consistent depressive symptoms below the threshold criteria is a chronic and disabling condition, with high risks (5, 6) that has a considerable impact on the quality of a patient's life (7). Though sub-threshold falls short of diagnostic criteria, it is as prevalent as more severe depression (8, 9). Additionally, previous studies also indicated that individuals with sub-threshold depression are at a high risk of developing MDD (10–12). Individuals with sub-threshold depression have an odds ratio of more than five for having a first lifetime episode of MDD (13).

Intervening at an early stage could help relieve symptoms and reduce the risk of major depression as well as prevent progression to other undesirable outcomes (8). However, no clinical guidelines or standards for sub-threshold depression have been established. Existing drug interventions have significant side effects (14, 15) and treatment normally causes an economic burden for middle class or low income households, and for the government (16). Currently experts do not recommend standard use of antidepressants as a first-line treatment to those with sub-threshold depression (17, 18), because there is less evidence to prove their effectiveness (19). A meta-analysis found that psychological therapy reduces adulthood depressive symptoms and prevents potential MDD with sub-threshold depression (7). Preventive psychotherapy-based intervention aimed at sub-threshold depression in children and adolescents also shows promising results (12). A previous study found that the psychotherapy intervention has more benefits for alleviating sub-threshold depression symptoms compared to medication management (20). Acupuncture as a major non-drug therapy has been well documented for the treatment of depression (21–23). A cross-sectional study found that depression is the second most common of the most commonly treated acupuncture indications in the United States (24). A single-center controlled trial of sub-threshold depression found that EA, counseling, and EA + counseling could significantly improve HAMD-17 scores, Center for Epidemiologic Depression scale, and WHO Quality of Life-Brief version scores of undergraduates students, and the remission rate is higher than that of the control group (p<0.05) (25). However, the clinical value of this finding is limited because it is a single-center clinical trial with a small sample size. Therefore, a high-quality multi-center RCT with large sample sizes is needed to further confirm this finding, which will provide reliable clinical evidence for the treatment of sub-threshold depression.

Therefore, this study intends to conduct a multicenter randomized controlled trial to compare the effectiveness among EA, counseling and the combined therapy in the treatment of patients with sub-threshold depression, and to further study the mechanism of EA and counseling in the treatment of sub-threshold depression, which will provide more options for the treatment of sub-threshold depression, and provide possible solutions for better efficacy.

## Methods

This protocol was designed according to the Standards for Reporting Interventions in Clinical Trials of Acupuncture (STRICTA) 2010 checklist (**Supplementary Table 1**), CONSORT 2010 checklist with the Non-pharmacological Trials Extension to CONSORT (**Supplementary Table 2**) and registered in the Chinese Clinical Trial Registry (ChiCTR1900028530).

### Trial Objective

We suspect that EA could alleviate the clinical symptoms of patients with sub-threshold depression as well as counseling. If EA is not only the placebo, the combination therapy will have a better effect, and may reduce the risk of conversion from mild to severe, as well as help determine whether patients with sub-threshold depression will need multiple therapies in the future. If acupuncture does no effect, the combination group will have the same clinical effect as the counseling group. Therefore, the objective of this trial is to evaluate the effectiveness of sub-threshold depression treatment by comparing the effects among EA, counseling, and combination therapy, as well as to further study the mechanism of EA and counseling.

### Trial Design

This study will be a multicenter, randomized, single blind clinical trial with three treatment groups (EA, counseling, and combination therapy). The flow chart in **Figure 1** shows more details regarding the clinical procedures. This study protocol has been approved by the Ethics Committee of the First Affiliated Hospital of Guangzhou University of Chinese Medicine, Affiliated Brain Hospital of Guangzhou Medical University, Guangdong Provincial Hospital of Chinese Medicine, and Guangdong Sanjiu Brain Hospital (NO. ZYYECK YJ [2019] 068).

**Figure 1 f1:**
[figure not shown]
Flow chart of study design.

### Setting

Investigators will conduct the trial in four hospitals in Guangzhou, China. These four hospitals are: The First Affiliated Hospital of Guangzhou University of Chinese Medicine; Affiliated Brain Hospital of Guangzhou Medical University; Guangdong Provincial Hospital of Chinese Medicine; and Guangdong Sanjiu Brain Hospital.

### Blinding

As a single-blinded trial, only outcome evaluators and statistical analysts will be blinded to treatment group. Evaluators and statistical analysts will not be allowed to participate in the treatment process of subjects and will be forbidden from knowing the grouping of subjects. Trial grouping information will be open to subjects, physicians, and data collectors. The analysts will generate a randomized sequence, only known by him or her, to allocate subjects accordingly to ensure the randomization of the grouping. The analyst will be responsible for the preservation and confidentiality of information and data and will prepare a backup of both electronic devices and paperwork. Special personnel will be in charge of those data and documentation. In addition, to ensure strict implementation of the blinded method in the test and reduce the bias of conclusions, physicians (psychologists and acupuncturists), outcome evaluators, data collectors, and statisticians will all be independent of each other and will have no communication during the test.

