### Randomization

Independent statisticians will use the block randomization method with SAS version 9.4 (SAS Institute. Inc., Cary, NC) to create a randomization table for each hospital. Randomization numbers will be sealed in opaque, sequentially numbered envelopes, and sent to each participating hospital (26). Random number envelopes will be kept in a double locker. If the participant meets the inclusion criteria and voluntarily signs the informed consent, the clinical research coordinator will send the sealed random number envelopes to the physician in order, who will open the envelope and allocate the qualified participants to the EA group, counseling group, and combined therapy group according to the random number.

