### Statistical Analysis

Statistical analysis will be performed by qualified statisticians in a blinded manner using Statistical Product and Service Solutions (SPSS) software (IBM Corporation, Version 21.0). An ITT analysis will be performed. The baseline comparability of the three groups will be assessed on demographic and clinical characteristics, as well as baseline data. Analysis of variance will be used to compare the mean changes between groups from baseline to each time point. The withdrawal of any subjects from clinical trials will be statistically described one by one. The missing data of a withdrawn patient will be randomly filled with the filling method based on the principle of multiple imputations (34). Continuous variables will be represented by mean ± standard deviation. The data before and after treatment in the group will be compared based on a paired *t*-test, and the comparison between groups will be performed using an independent sample *t*-test. When data are not normally distributed, a Wilcoxon rank sum test or Fisher's exact test will be performed. Multiple measurements of the same indicator at different times will use repeated measures data analysis of variance. Categorical variables will be expressed as frequency (%). Two-tailed *p* values < 0.05 will be considered as statistically significant. Safety will be assessed by adverse events and tabulations of adverse drug reactions and descriptive statistics will be performed. Age and intervention assessment are continuous variables, and their correlation will be analyzed using Pearson correlation coefficients. Treatment duration and gender are graded variables, and the spearman correlation coefficient will be used for the correlation analysis of the intervention assessment. To further evaluate the credibility of the blind method. We will evaluate the implementation of the blind method by trial participants' guesses about the allocation of treatment plans, that is, forcing evaluators and statistical analysts to guess the groups to which the subjects are assigned, and then calculate the Blinding Index Scale based on the guess results (39). In order to balance the heterogeneity of patients from different research centers, we will first analyze the differences between the clinical effects of different interventions in each subcenter. If the conclusions of the subcenters are consistent, there will be no central effect. If the conclusions of the sub-centers are inconsistent, a logistic regression analysis will be performed, and the center will be adjusted as a covariate to analyze the results of interventions and clinical assessment (40, 41).

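### The Blinding section requires analysts not to know the grouping, yet has them generate and alone know the randomisation sequence, so blinded analysis is not assured as written

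*Protocol article*

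**What the plan says.** Three sections of the protocol article deal with this role.

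- **Blinding.** The trial is single blind, and "only outcome evaluators and statistical analysts will be blinded to treatment group". Both roles "will be forbidden from knowing the grouping of subjects". The same paragraph then says: "The analysts will generate a randomized sequence, only known by him or her, to allocate subjects accordingly to ensure the randomization of the grouping". It adds: "The analyst will be responsible for the preservation and confidentiality of information and data". The next sentence puts dedicated staff in charge of the data and documents. The paragraph ends by separating the trial's functions: therapists, "outcome evaluators, data collectors, and statisticians will all be independent of each other", with no communication between them during the trial.
- **Randomization.** "Independent statisticians will use the block randomization method with SAS version 9.4", with one table per hospital. The allocations go to the hospitals in sealed envelopes, which are used in order.
- **Statistical Analysis.** Qualified statisticians are to analyse the data blinded. The success of blinding is to be checked by "forcing evaluators and statistical analysts to guess the groups to which the subjects are assigned" and computing a blinding index from the guesses.

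**The concern.** Whoever writes the allocation list and is the only one to know it cannot also be barred from knowing who is in which arm. The Blinding section assigns both positions to a role with the same name.

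The blind matters in this trial because few others exist. Participants, physicians and data collectors all know the allocation, so evaluators and analysts are the only two blinded roles. The secondary outcomes SDS, SAS and PSQI are completed by participants who know their treatment. Evaluator blinding gives these scores no protection, and analyst blinding is the only claimed blind that bears on how they are handled and analysed.

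Some choices are also made after the data are seen. The test depends on whether the data look normal, and adjustment for centre depends on whether the centres' conclusions agree. An analyst who can link subjects to arms could be influenced in such choices, even without intent.

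**Working it through.** No arithmetic decides this point, and the plan gives no figure to reproduce. The check is to set the statements side by side.

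**Step 1: the Blinding section on its own.**

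| Question | Answer in the Blinding section |
|---|---|
| May analysts know the grouping? | No, it is forbidden |
| Who generates the sequence? | The analysts |
| Who knows the sequence? | Only the analyst |

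The first answer cannot hold together with the other two if "analyst" means the same role throughout, and the section gives no second meaning.

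**Step 2: does holding the sequence reveal the grouping?** Under Randomization there is one list per hospital and the envelopes are used in order. A subject's hospital and place in the enrolment order therefore point to a line of the list. Someone with the list and ordinary trial data can recover the arm.

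**Step 3: does another section resolve it?** The Randomization section names independent statisticians. Two readings are possible.

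- *They are the same people as the analysts.* The analysts then hold the key, and the blinded analysis is not blinded.
- *They are different people.* The Blinding and Randomization sections then name different generators of the list, and the Blinding section is wrong about who knows it.

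The text does not choose between these readings. The closing sentence on independence lists statisticians as a single group. It separates them from therapists, evaluators and data collectors, but does not separate the randomising statistician from the analysing one. Under either reading a sentence has to change.

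**Step 4: the blinding index.** The index takes guesses from two roles. With three arms of 46 in a total of 138, a person with no information who guesses at random is right for about 46/138 = 1/3 of subjects. A person who holds the list can be right for all 138 with no leak having occurred. That result would show possession of the list and say nothing about concealment. The evaluators do not hold the list under either reading, so their guesses remain informative.

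**Step 5: what the sentence leaves intact.** Evaluators are still kept from the allocation. The sealed envelopes still conceal the next assignment from those who enrol.

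**The case against.** The strongest reply is that this is loose naming. The Randomization section is the operative text and gives the list to independent statisticians. The Statistical Analysis section speaks separately of qualified statisticians working blinded. The Blinding section may use its word for analysts to mean the independent statisticians, and the remark about sole knowledge may be meant to describe allocation concealment. This is plausible, and the text does not settle that list-holder and analyst are one person. But it does not say that they are different either, and a contradiction within one paragraph still has to be corrected.

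Other parts of the reply stand and limit the point:

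- A reader might infer that the whole blinding index is worthless. The text does not support this, because only the analysts' part is affected.
- A reader might infer that the analyst alone has custody of the data. The Blinding section also puts dedicated staff in charge of them.
- A reader might infer that the analyst decides who is eliminated. The elimination and withdrawal criteria do not assign that decision, and the analysis is stated to be by intention to treat.
- Multiple imputation is named in advance, the rank test is tied to non-normality and not to arm, and the centre rule would depend on the data even with coded arms. The article does not present analyst blinding as the safeguard for these choices.

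**Conclusion.** The contradiction is real and lies in the current text. It does not come from condensing a longer document or from an analysis plan that is not shown, because the article makes two incompatible statements about one role. If the Blinding section is followed as written, one of the two claimed blinds is defeated and the analysts' part of the blinding index cannot measure concealment.

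That conclusion rests on one assumption: that the analysts named as generators are those who analyse the data. If they are not, what remains is a conflict between the Blinding and Randomization sections over who generates and holds the list. A reader might go further and conclude that the trial's analysis is in fact unblinded, or that its results will be biased. The article shows neither; it shows only that blinded analysis is not assured. The passages should be reconciled before any analyst receives data.

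**What to change.** 1. Amend the Blinding section so that the independent statistician of the Randomization section generates and holds the sequence and takes no part in the analysis.
2. Give the analysts a dataset with arms coded A/B/C until the analysis sets, the imputation and the primary analysis are fixed.
3. Use the same role names in Blinding, Randomization and Statistical Analysis, so that the randomising and the analysing statistician can be told apart.
4. Keep analysts in the blinding index only if they do not hold the list. Once they are truly blinded their guesses are informative, and there is no need to drop them.

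The cost is small: wording, a coded dataset, and a clear split of roles among the statisticians already named. If the same people now fill both roles and cannot be divided, one further person may be needed to hold the list. Sample size, visits and treatment do not change.

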### Randomization

Independent statisticians will use the block randomization method with SAS version 9.4 (SAS Institute. Inc., Cary, NC) to create a randomization table for each hospital. Randomization numbers will be sealed in opaque, sequentially numbered envelopes, and sent to each participating hospital (26). Random number envelopes will be kept in a double locker. If the participant meets the inclusion criteria and voluntarily signs the informed consent, the clinical research coordinator will send the sealed random number envelopes to the physician in order, who will open the envelope and allocate the qualified participants to the EA group, counseling group, and combined therapy group according to the random number.

### Participants

Participants will be recruited by advertisement and doctor referrals from psychology department clinics. Interested individuals can contact research assistants by email or phone. A series of criteria and prerequisites will be sent to the prospective volunteers for filtering the most eligible subjects. First, registration information and pre-selection query forms with Self-rating Depression Scale (SDS), Pittsburgh Sleep Quality Index (PSQI), and Self-rating Anxiety Scale (SAS) will be sent to registered volunteers. Volunteers will be required to complete the form as a first-round selection prior to scheduling a first visit. This visit will further screen and evaluate a volunteer's eligibility according to inclusion criteria (**Table 1**). Research assistants will collect signed consent forms from volunteers who meet all prerequisites and agree to participate in the trial. Patients will not be included in the study if they meet one of the exclusion criteria (**Table 2**).

**Table 1 T1:** Inclusion criteria.

No	Item	Answer
1	18<age<55	□Yes
		□No
2	Presence of ≥ 1 but < 5 symptoms required for the diagnosis of major depression as detailed in the Diagnostic Statistical Manual of mental disorders (DSM-V), including loss of enjoyment/interest, marked tiredness or reduction of energy, agitation or psychomotor retardation, feelings of worthlessness or guilt, sleep disorders, reduced concentration, loss of appetite and body weight, loss of libido, recurrent suicidal thoughts;	□Yes
		□No
3	symptoms lasting at least 2 weeks	□Yes
		□No
4	BDI-II score≥14 points (24)	□Yes
		□No
5	HAMD-17 score: 7 points ≤ HAMD total score < 17 points (25)	□Yes
		□No

**Table 2 T2:** Exclusion criteria.

No	Item	Answer
1	Patients diagnosed with depression, previous mental illness, or organic mental disorders	□Yes
		□No
2	Patients suffering from serious diseases such as heart, brain, liver, kidney, or hematopoietic system disease	□Yes
		□No
3	Women during pregnancy and lactation or women of childbearing age who have fertility intentions	□Yes
		□No
4	Patients with depressive episodes caused by psychoactive substances and non-addictive substances	□Yes
		□No
5	Patients prescribed other drugs or therapies for treating depression during the trial	□Yes
		□No
6	Individuals addicted to alcohol or other drugs	□Yes
		□No
7	Patients with strong suicidal ideation	□Yes
		□No
8	Patients who are participating in other clinical trials at the same time	□Yes
		□No
9	Patients who have undergone antidepressant treatment within 1 week before the test	□Yes
		□No
10	Skull defects in the acupuncture site, or a surgical scar or skin infection that affects the treatment	□Yes
		□No
11	Patients who are allergic to acupuncture or faint when they are stuck with needles	□Yes
		□No
12	Age older than 55 years or younger than 18 years.	□Yes
		□No

